#### Full trial

For the full study, the sample size was calculated for a two-sided *t* test comparing two independent samples. Based on previous follow-up data from the Alberta Children’s Hospital Diabetes Clinic, the mean score of HbA1C at baseline in both groups will be estimated to be 8.4 with a standard deviation of 1.3 for each group. A clinically significant change in absolute HbA1c of 0.5 will be used, as this threshold has been used in previous drug trials to demonstrate effectiveness in diabetes. For a power of 80 % and an alpha of 0.05, the number of subjects needed per arm of the study is 107. If we assume a drop-out rate of 20 %, then approximately 135 subjects per arm of the study will be required in a fully powered study.

### Analysis

Analysis will be performed using SPSS 22.0 software (IBM, New York, USA). Results will be considered statistically significant if *p* ≤ 0.05. Baseline descriptive data between the control and intervention group will be compared using chi-square for categorical variables and *t* tests for continuous variables. The primary outcome of HbA1c will be expressed as mean HbA1c values with standard deviations, and a two-sided *t* test will be used to compare HbA1c between placebo and prebiotic groups. Differences between the placebo and prebiotic groups’ C-peptide, inflammatory markers (IL-6, IFN-gamma, TNF-alpha, and IL-10), GLP-1, GLP-2 and intestinal permeability will be compared using a two-sided *t* test. Adverse events will be presented as the proportion of each event seen in each group (placebo and prebiotic). An intent-to-treat analysis will be used with the last data point carried forward for missing data. A secondary analysis will also be performed on a per-protocol basis with all subjects who have completed the intervention and are reported to be compliant with ≥80 % of the prebiotic or placebo packets consumed.

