### Randomization

Participants will be randomized via computer-generated numbers to intervention or placebo control in a 1:1 ratio. The intervention and placebo groups will not be matched (e.g. age, duration of T1DM, etc.). An investigator not involved in running the study will prepare the randomization sequences and have the random allocation sequence in numbered envelopes in a secure location that will be opened only once a participant has consented and enrolled in the study. The participants, trial coordinator and research staff who enroll the patients will remain blinded to the participants’ group assignment. Participants will be asked at the end of the study to which group they believed they were assigned.

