#### Glycemic control, inflammatory markers, GLP-1 and GLP-2

Blood will be collected at baseline, 3 months and 6 months for serum C-peptide, HbA1c, serum inflammatory markers (IL-6, IFN-gamma, TNF-alpha and IL-10), GLP-1 and GLP-2. Serum will be sent to Calgary Laboratory Services (Calgary, AB, Canada) for measurement of HbA1c by turbidimetric inhibition immunoassay (Roche Integra 800 CTS, Basel, Switzerland) and serum C-peptide by chemiluminescent assay (Siemens Immulite 2000, Erlangen, Germany). Serum inflammatory markers will be analysed by Milliplex Human Cytokine Magnetic Bead Multiplex kits (Millipore, St. Charles, MO, USA). GLP-1 and GLP-2 will be measured with ELISA kits (Millipore, St. Charles, MO, USA).

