
### Sample size

#### Internal pilot

The initial pilot study will aim to test the feasibility of a fully powered studied in children with type 1 diabetes. To test feasibility in this pilot study, we will enroll 15 subjects per arm. If we assume a drop-out rate of 20 % (12 subjects completing the study in each arm), power of 80 %, and alpha of 0.05 and a standard deviation of 1.3 for HbA1c, then with the pilot study we would be able to detect a mean difference in the absolute HbA1c of 1.5 between the placebo and prebiotic groups.

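### The primary HbA1c analysis is an unadjusted t test on follow-up values, so the precision available from the measured baseline HbA1c is forgone

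*Protocol article*

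**What the plan says.** The Analysis section puts the primary outcome on the scale of HbA1c values: "The primary outcome of HbA1c will be expressed as mean HbA1c values with standard deviations". The comparison is then a two-sided t "test will be used to compare HbA1c between placebo and prebiotic groups". No covariate and no change score is named. The other continuous outcomes (C-peptide, inflammatory markers, GLP-1, GLP-2, intestinal permeability) get the same two-sided t test.

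Baseline HbA1c is available. The section on glycemic control and blood markers states: "Blood will be collected at baseline, 3 months and 6 months for serum C-peptide, HbA1c". Baseline values have two stated or implied uses. One is a between-arm comparison of baseline characteristics ("Baseline descriptive data between the control and intervention group will be compared using chi-square for categorical variables", with t tests for continuous variables). The other is as the carried-forward value for a child with no later measurement.

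The Randomization section does not balance baseline HbA1c. Participants are "randomized via computer-generated numbers to intervention or placebo control in a 1:1 ratio", and it adds: "The intervention and placebo groups will not be matched". No stratification is described. In the Internal pilot section, "we will enroll 15 subjects per arm".

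Both sample size sections use an SD of 1.3. The Full trial section words its target of 0.5 as a change, but the SD is that of HbA1c itself (mean 8.4), and the calculation is for two independent samples.

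**The concern.** HbA1c differs between children and tends to persist within a child, so a child's baseline value predicts part of the follow-up value. An analysis that leaves baseline out treats that predictable part as noise. Two things follow.

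- **Efficiency.** The pilot can detect only a larger difference than it needs to, and the projected full trial asks for more children than it needs to.
- **Chance imbalance.** With 12 to 15 children per arm and no stratification, the arms may well differ at baseline by an amount comparable to the plan's own target of 0.5. The unadjusted estimate carries part of that gap. A baseline significance test may flag the gap but does not correct the treatment comparison.

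HbA1c is the outcome of the stated primary objective, and the pilot is meant to inform the full trial, so both effects matter here.

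**Working it through.** **Inputs.** SD 1.3, two-sided alpha 0.05, power 80%, difference 0.5 for the full trial, 20% drop-out, and 15 enrolled and 12 completing per arm in the pilot (Sample size sections). The correlation r between baseline and follow-up HbA1c is not in the document, so a range is assumed. The SD is taken as equal at baseline and follow-up.

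**Step 1: reproduce the plan's figures.**

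- Full trial: n per arm = 2 × (1.960 + 0.842)² × 1.3² / 0.5² = 106.1, rounded up to 107, as stated. The noncentral t gives 108. With drop-out, 107 / 0.8 = 133.75, or 134, against about 135 stated.
- Pilot: detectable difference = (1.960 + 0.842) × 1.3 × √(2/12) = 1.49, against 1.5 stated. The noncentral t gives 1.56.

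Both figures fit an unadjusted comparison of HbA1c values.

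**Step 2: adjust for baseline.** ANCOVA leaves a residual SD of 1.3 × √(1 − r²), so the variance removed is r². The required n scales by (1 − r²) and the detectable difference by √(1 − r²), using the normal approximation throughout.

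| r (assumed) | variance removed | residual SD | pilot detectable difference, 12 per arm | full trial n per arm (after 20% drop-out) |
|---|---|---|---|---|
| unadjusted | – | 1.30 | 1.49 | 107 (134) |
| 0.3 | 9% | 1.24 | 1.42 | 97 (122) |
| 0.5 | 25% | 1.13 | 1.29 | 80 (100) |
| 0.6 | 36% | 1.04 | 1.19 | 68 (85) |
| 0.7 | 49% | 0.93 | 1.06 | 55 (69) |
| 0.8 | 64% | 0.78 | 0.89 | 39 (49) |

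With the noncentral t, and allowing for the estimated covariate and its degree of freedom, the pilot figures are 1.56 unadjusted and 1.38, 1.28, 1.14 and 0.96 at r = 0.5, 0.6, 0.7 and 0.8. If the full trial stayed at 107 per arm, power for 0.5 would rise from 80% to 90% at r = 0.5 and to 98% at r = 0.7.

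**Step 3: chance imbalance.** The SE of the baseline mean difference is 1.3 × √(2/n).

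- 15 per arm: SE 0.47; probability of a gap above 0.5 in either direction = 2 × [1 − Φ(0.5/0.475)] = 29%.
- 12 per arm: SE 0.53; the same probability is 35%.

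Given a baseline gap d, the expected unadjusted difference is the treatment effect plus r × d. A gap of 0.5 therefore shifts the estimate by 0.25 at r = 0.5 and by 0.40 at r = 0.8. For imbalance alone to shift it by 0.5, the gap must exceed 0.5/r. That has probability 4% (r = 0.5) to 19% (r = 0.8) at 15 per arm, and 6% to 24% at 12 per arm.

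**Step 4: is a change score enough?** Its SD is 1.3 × √(2 − 2r), so n scales by (2 − 2r). This gives 128 per arm at r = 0.4, 107 at r = 0.5, 64 at r = 0.7 and 43 at r = 0.8. It beats the raw comparison only when r exceeds 0.5, and ANCOVA needs fewer children at each of these values (90, 80, 55, 39).

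**The case against.** The strongest reply is that nothing here is an error. Under randomisation the unadjusted t test keeps its type I error and is unbiased on average, and its standard error already includes the variation caused by baseline imbalance. The stated sizes reproduce for the planned test and would be conservative under ANCOVA. The Internal pilot section also presents the 15-per-arm stage as a test of feasibility. All of this stands, and it sets the severity.

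Two stronger readings are tempting, and the document supports neither.

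- A reader might infer that most of the available precision is thrown away. The loss is r² of the variance, and more than half is lost only if r exceeds about 0.71. No r is given.
- A reader might infer that a chance baseline gap passes whole into the estimate and is reported as a treatment effect. Only the fraction r passes. The 29% and 35% are probabilities of a gap at baseline, not of an equal error in the result. The exception is a child with no follow-up value, whose carried-forward baseline enters in full.

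Eligibility adds a caveat. Table 1 excludes children with any HbA1c above 10% in the previous 6 months, and the document does not say whether the SD of 1.3 was taken after that exclusion. If it was not, and HbA1c is roughly normal with mean 8.4 and SD 1.3 (an assumption), truncation at 10 gives an SD of about 1.09. The chance of a 0.5 gap then becomes about 21% at 15 per arm and 26% at 12. The restricted range would also lower r, for example from 0.7 to about 0.63.

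These points reduce the gain but do not remove it: even at r = 0.3 the full-trial size falls from 107 to 97 per arm.

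**Conclusion.** The point holds as forgone efficiency. The planned test is valid and the sample sizes match it, but it leaves out a baseline measurement that the trial already takes. If r lies between 0.5 and 0.8, about 25% to 64% of the variance could be removed. That is equivalent to reducing the full trial from 107 to between 80 and 39 per arm, or the pilot's detectable difference from about 1.5 to between about 1.3 and 0.9. The figures rest on the assumed r, on an SD of 1.3 that the HbA1c exclusion may lower, and on equal SDs at baseline and follow-up. This is a recommended improvement. It is not a must-fix, because the document contains no wrong figure and no invalid test on this point.

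**What to change.** Make the primary analysis an ANCOVA of follow-up HbA1c on treatment group with baseline HbA1c as covariate, and report the adjusted difference with its 95% confidence interval. Use the same form for the other continuous outcomes measured at baseline. Do not substitute a simple change score, for the reason in step 4 of the working.

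Before sizing the full trial, estimate r and the SD from the clinic's existing HbA1c data, restricted to eligible children, or from the pilot. Then base the calculation on the residual SD.

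The cost is a change to the analysis wording and one degree of freedom, with no new data. The Trial status section says recruitment has only just begun, so the covariate can be fixed before outcomes are known. Adding it after seeing an imbalance would be a post hoc choice.

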#### Intestinal permeability

Intestinal permeability will be assessed at baseline, 3 months and 6 months. Participants will consume a regular evening meal and then 3 hours later, prior to bedtime, drink a solution containing lactulose (5 g), mannitol (2 g) and 3-O-methylglucose (5 g) in 200 mL of water (Biosource, Canada). All urine for the following 12 hours will be collected with 5 mL thymol in the storage container for preservation, and stored frozen. High-performance liquid chromatography (HPLC) will be used to analyse urine samples for the lactulose, mannitol and 3-O-methylglucose content. Urine samples will be filtered through a 0.4-μm filter and diluted as necessary. Samples will be deionized and injected into an ion exchange column and eluted with NaOH at a flow rate of 0.4 mL/min with concentrations ranging from 400 to 600 mM. Peaks will be detected using pulse and amperometric detection in a Dionex HPLC. The fraction of the ingested dose recovered in the urine sample will be calculated and compared between the two groups [26, 27].

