#### Gut microbial profiling

Stool samples will be collected at baseline, 3 months and 6 months as previously described [14, 20]. Participants will be provided with a Bristol stool chart and asked to mark down the type of stool (type 1 to type 7). Participants will be provided a stool collection kit and will be instructed on proper methods for stool collection. One tablespoon of stool will be placed in a pre-labelled sterile conical tube, placed in a biohazard bag and stored in the home freezer (–20 °C). Participants will bring samples to the laboratory up to 3 days from collection on ice, and then the samples will be stored in the laboratory freezer at –80 °C until analysed. Total bacterial DNA will be extracted from stool samples using the FastDNA Spin Kit for Feces (MP Biomedicals, Lachine, QC, Canada) followed by ethanol precipitation purification. DNA will be quantified using Qubit dsDNA assay (Promega, Madison, WI, USA) and diluted to 5 ng/μL concentration. Microbial composition will be determined as per our previously published protocol [28] following Illumina’s 16S rRNA amplicon sequencing protocol on the MiSeq platform (Illumina, San Diego, CA, USA). The V3 and V4 regions of the 16S rRNA gene will be amplified using 2.5 μL (5 ng/μL) microbial DNA, 5 μL (1 μM) of gene-specific primers and 12.5 μL 2x KAPA HiFi Hotstart Ready Mix (KAPA Biosystems, Boston, MA, USA). Following amplification, the PCR product will be purified (Ampure XP beads, Beckman Coulter, Mississauga, ON, Canada) and the amplicon size confirmed. Dual-indexed barcodes will be attached to amplicon targets in a second PCR stage. The final PCR product will be purified (Ampure XP beads, Beckman Coulter, Mississauga, ON, Canada) and quantified using the Qubit dsDNA assay (Promega). Amplicon size will be assessed using a D1000 TapeStation (Agilent Technologies) assay and samples normalized to 4 nM using 10 mM Tris pH 8.5. After pooling barcoded libraries, samples will be denatured and diluted to a final concentration of 4 pM, and a final product containing 10 % PhiX will undergo dual-indexed paired 300 bp sequencing on the MiSeq using Reagent kit v3 (Illumina). Paired-end reads will be merged using PEAR (Paired-End read merger) [29], and data analysis will be performed using the Quantitative Insights into Microbial Ecology (QIIME) pipeline version 1.9.1 [30]. Operational taxonomic units (OTUs) will be picked using UCLUST [31] with a 97 % sequence identity threshold followed by taxonomy assignment using the latest Greengenes database (http://greengenes.secondgenome.com). To evaluate beta diversity, principal coordinate analysis (PCoA) on weighted UniFrac distances will be performed on all OTUs using QIIME. Alpha diversity will be measured by calculating the Shannon index, Simpson index and Chao1 metrics using QIIME [30]. A false discovery rate will be used to control for type 1 error. Given that 16S rRNA sequencing generates relative abundance data, we will also quantify the abundance of select microbial groups (e.g. *F. prausnitzii*, *Bifidobacterium* spp., total bacteria) with quantitative PCR according to our previous work [14, 20] using the Bio-Rad iCycler (Bio-Rad Inc., Mississauga, ON) and group-specific primers.

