## Discussion

DM1 in children is a chronic disease with the current mainstay of treatment being subcutaneous insulin administration multiple times a day, frequent capillary glucose monitoring and monitoring/counting carbohydrate intake at all meals and snacks. The management regimen in DM1 is invasive and labor intensive and may not always result in optimal glycemic control. Therefore, the addition of a simple, oral supplement such as a prebiotic to improve glycemic control would be very beneficial in this population.

Based on animal and human studies to date [9], we anticipate that a change in gut microbiota, gut permeability and inflammatory markers could occur over the course of several weeks of prebiotic supplementation. Hence, we anticipate that changes in these parameters will be detectable at the 3-month follow-up. The change in HbA1c will likely lag behind — as the life span of glycosylated red blood cells is 3 months, any improvement in glycemic control as a result of the 3-month prebiotic treatment may not be fully reflected at the 3-month follow-up, but may only become detectable at the 6-month follow-up. We will reassess all these parameters at 6 months to determine the persistence of effects and whether continued consumption of prebiotics is necessary to maintain the changes in gut microbiota, gut permeability and inflammatory markers observed.

Kellow et al. [9] published a systematic review on the metabolic benefits of prebiotics in human randomized controlled trials. Meta-analysis indicated a statistically significant effect of prebiotics on reduction in post-prandial glucose and post-prandial insulin levels. Conflicting results were seen in studies looking at fasting glucose, fasting insulin and HbA1c. No pediatric studies or populations with DM1 were identified for inclusion in this systematic review.

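### Eight mechanistic markers get plain two-sided t tests at 0.05, with no multiplicity rule and no stated use of baseline: up to 56% chance of a false positive if tested at both visits, plus avoidable loss of precision

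*Protocol article*

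**What the plan says.** The Analysis section sets one threshold for everything: "Results will be considered statistically significant if" p ≤ 0.05. After the primary HbA1c comparison it says that C-peptide, the four inflammatory markers, "GLP-1, GLP-2 and intestinal permeability will be compared using a two-sided" t test. Counting permeability once, that is eight outcomes: C-peptide, IL-6, IFN-gamma, TNF-alpha, IL-10, GLP-1, GLP-2 and permeability.

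All have a baseline and two follow-up measurements. For blood: "Blood will be collected at baseline, 3 months and 6 months for serum C-peptide" and the other markers. For the sugar test: "Intestinal permeability will be assessed at baseline, 3 months and 6 months". The Discussion expects the mechanistic changes to be visible at 3 months and adds: "We will reassess all these parameters at 6 months to determine the persistence of effects".

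The only statement on multiplicity is in the Gut microbial profiling section: "A false discovery rate will be used to control for type 1 error". The Intestinal permeability section gives three probe sugars and says: "The fraction of the ingested dose recovered in the urine sample will be calculated and compared between the two groups". It names no single sugar and no ratio as the readout.

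The objectives, at the end of the Background, place these markers below HbA1c (primary) and microbiota composition (secondary), as further aims.

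**The concern.** The authors control the error rate for taxa but give eight mechanistic markers a bare 0.05 each. The Background offers the pilot as proof of concept for later trials, and the postulated chain runs from microbiota through permeability and inflammation to glycaemia. A chance result in one cytokine or one sugar could be read as support for a link in that chain and shape the full trial.

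The method is also inefficient where information is scarce. Baseline values are collected, but the stated comparison does not use them. Positive concentrations in 12–15 children per arm are often skewed, and then one or two high values can dominate a mean. Recovery of a single sugar falls with any urine missed during a 12-hour home collection, whereas a ratio of two sugars swallowed together is largely protected from that.

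**Working it through.** **Inputs from the article.** Alpha 0.05; eight outcomes (ten if each sugar is tested separately); two follow-up visits; 15 per arm enrolled, 12 completing. Correlations, log-SDs and the true effect on a marker are not given, so they are assumed below.

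**The plan's own figure.** The article gives no error rate for the markers. Its pilot figure is an HbA1c difference of 1.5 with 12 per arm, SD 1.3, 80% power. Check: 1.3 × √(2/12) × (1.960 + 0.842) = 1.49, which reproduces it (1.56 with the exact t distribution).

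**Chance of at least one false positive, no true effects, independent tests:** 1 − 0.95^k.

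- k = 8 (one visit): 33.7%; expected number 8 × 0.05 = 0.4
- k = 16 (both visits): 56.0%; expected number 0.8
- k = 20 (three sugars, both visits): 64.2%; expected number 1.0

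The figure passes one half only from 14 independent tests (51.2%; 13 give 48.7%).

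**Allowing for correlation.** Simulation of 16 pooled t tests, normal data, 15 per arm, 20,000 replicates:

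| Between-visit correlation | Between-outcome 0 | 0.2 | 0.3 | 0.5 |
|---|---|---|---|---|
| 0 | 56% | 54% | 52% | 44% |
| 0.3 | 55% | 52% | 50% | 45% |
| 0.5 | 53% | 51% | 49% | 42% |
| 0.7 | 50% | 49% | 46% | 39% |

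With 12 per arm the results are nearly the same. The expected number of false positives stays at 0.8, because correlation does not change it.

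**Allowing for skewness.** With lognormal data (log-SD 1) tested untransformed, each test rejects about 3.5–3.7% of the time, and the chance of at least one false positive in 16 is 33–45%. Skewness therefore costs power; it does not add false positives.

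**Power, raw against log scale.** 12 per arm, true ratio 0.4 (a 60% reduction), so the log difference is |ln 0.4| = 0.916. All values here are assumed.

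- Log-SD 0.8: standardised difference 0.916/0.8 = 1.15; power about 76% on the log scale and 62% raw, a loss of 14 points
- Log-SD 1.0: standardised difference 0.92; power about 57% on the log scale and 38% raw, a loss of 19 points

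**Baseline.** With baseline-to-follow-up correlation r, the error variance relative to comparing follow-up values alone is 1 − r² for ANCOVA and 2(1 − r) for change from baseline. For assumed r = 0.5 these are 0.75 and 1.00; for r = 0.7 they are 0.51 and 0.60. ANCOVA has the smaller variance in both cases.

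**Permeability.** If a fraction f of the urine is captured and both sugars are lost in the same proportion, lactulose recovery is f·L/5 and mannitol recovery is f·M/2, where L and M are the grams excreted. The ratio is (L/5)/(M/2), and f drops out. Each single recovery still carries f.

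**The case against.** The strongest reply is that these are further aims of a feasibility pilot. Unadjusted testing of such outcomes is common, and it leaves the primary conclusion untouched. That stands. It is why an exploratory label is an adequate answer and formal adjustment is optional.

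A second reply is that much of the count is inference. The Analysis section names no visit, does not say whether values or changes are compared, and does not say that each sugar is tested. The Discussion can be read as testing at 3 months and only describing persistence at 6. That also stands: on that reading there are eight tests and the figure is 34%.

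Third, the article does not say that the data stay untransformed. Transformation may be settled in a fuller document that is not shown, so the absence of a log scale is not itself an error. Likewise, computing fractional recoveries does not rule out a ratio, since a ratio is built from them. In a blinded randomised trial, lost urine should mostly add noise and not bias. These points limit the claim. They do not change the fact that the method actually stated is a plain two-group t test at 0.05, with false-discovery control confined to another section.

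A reader might go further and infer that a false mechanistic claim is more likely than not, or is the expected outcome. The documents do not support that. It needs at least 14 effectively independent tests and no true effect on any marker. Correlation takes the 16-test figure to either side of one half, and on skewed raw data it was below one half in every case run. The 64% figure also needs three separately tested sugars, which the article does not specify.

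**Conclusion.** The point holds as a recommended improvement. Eight markers are judged at 0.05 each without the error control given to microbiota, and the stated test makes no use of baseline values that are collected anyway.

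If all eight are tested at both follow-up visits and none has a true effect, the chance of at least one false positive is at most 56%. It is about 40–56% under the assumed correlations (up to 0.5 between outcomes and 0.7 between visits), 34% at one visit, and 33–45% for 16 tests on skewed raw data. Every one of these is several times the nominal 5%.

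The power loss of about 14–19 points depends on right-skewed markers with log-SD 0.8–1.0 and a 60% reduction, none of which comes from the article. The loss from ignoring baseline applies if follow-up values alone are compared, which is the plain reading of the sentence. The primary HbA1c comparison is not affected.

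**What to change.** Revise the Analysis section as follows.

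- Name 3 months as the visit for between-group comparison of the mechanistic markers. Treat 6 months as a descriptive account of persistence.
- Analyse each marker by ANCOVA on the log scale with its own log baseline as covariate, and report the ratio of geometric means with a 95% CI. Use a rank-based method where many values lie below the detection limit.
- Make the log lactulose:mannitol recovery ratio the main permeability readout, with the individual sugar recoveries, including 3-O-methylglucose, as supportive.
- Label these comparisons exploratory and make no significance claim from them. Alternatively, extend the false-discovery control already used for microbiota to this family.

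No new participants, samples or assays are needed. The cost is slightly more analysis work and fewer nominally significant markers. Adjustment, if chosen over the exploratory label, would also reduce power for each marker in a small trial.

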### Intervention

Participants will be randomized to receive either placebo (maltodextrin 3.3 g orally/day; Agenamalt 20.222, Agrana Starch, Konstanz, Germany) or prebiotic (oligofructose-enriched inulin 8 g orally/day; Synergy1, Beneo, Mannheim, Germany). Inulin and oligofructose are approved as food ingredients in Canada and have been used previously in clinical trials [8, 25]. Both the prebiotic and placebo will be provided to participants in powder form in identical foil pre-weighed packets. Participants will be instructed to mix the packet with 250 mL of water until dissolved and to drink it 15–20 minutes prior to their evening meal. For the first 2 weeks, participants will be asked to only take half of the dose in order to minimize gastrointestinal side effects, and then they will take the full dose for the remaining 10 weeks.

Participants will be asked to record any diabetes-related or gastrointestinal adverse reactions, i.e. frequency of mild hypoglycemia (symptoms of hypoglycemia with a blood glucose less than 4 mmol/L and able to self-treat with oral rapid-acting carbohydrate), severe hypoglycemia (symptoms of hypoglycemia with a blood glucose less than 4 mmol/L but requires assistance with treatment due to decreased level of consciousness or has a seizure), diabetic ketoacidosis or flatulence. At the end of the 12 weeks, participants will be asked to return any remaining packets of placebo or prebiotic in order to assess for compliance. Telephone contact from a member of the research team will occur monthly to encourage compliance and recording of adverse reactions.

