### Data collection

Study visits will be coordinated with diabetes clinic visits; the data to be collected are outlined in Table 2. Demographic information will be collected at baseline. Anthropometric measures and assessment of insulin regimens, frequency of diabetic ketoacidosis (DKA) in previous 3 months, frequency of severe hypoglycemia in previous 3 months and average number of mild hypoglycemic episodes per week in the preceding 3 months will be assessed at baseline, 3 months and 6 months.

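### Mild hypoglycemia is collected as a weekly frequency, but the only stated adverse-event summary is a proportion, which may hide a rise if episodes are common; the mild and severe definitions also leave one kind of episode unclassified.

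*Protocol article*

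**What the plan says.** In the protocol article, three places bear on this.

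- **Intervention.** The diary asks for frequency, not just occurrence: "Participants will be asked to record any diabetes-related or gastrointestinal adverse reactions, i.e. frequency of mild hypoglycemia". Mild hypoglycemia is defined as "symptoms of hypoglycemia with a blood glucose less than 4 mmol/L and able to self-treat with oral rapid-acting carbohydrate". Severe hypoglycemia has the same symptom and glucose condition, but the child "requires assistance with treatment due to decreased level of consciousness or has a seizure".
- **Data collection.** The clinic visits gather "frequency of severe hypoglycemia in previous 3 months", and for mild episodes the "average number of mild hypoglycemic episodes per week in the preceding 3 months will be assessed at baseline, 3 months and 6 months".
- **Analysis.** All adverse events fall under one sentence: "Adverse events will be presented as the proportion of each event seen in each group (placebo and prebiotic". It does not say whether the denominator is participants or events. The section names t tests for HbA1c, C-peptide, the inflammatory markers, GLP-1, GLP-2 and permeability, but nothing that uses the hypoglycemia frequencies.

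The safety objective at the end of the Background names severe hypoglycemia and diabetic ketoacidosis (DKA). It does not name mild hypoglycemia.

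**The concern.** Mild hypoglycemia can recur many times in one child. A proportion of children with at least one episode ignores how many episodes each child had, and if most children have at least one, it has little room to move. The primary objective concerns HbA1c, and more frequent hypoglycemia could accompany or contribute to a lower HbA1c. A reader therefore needs the frequency by arm to interpret any benefit. The data for this are already to be collected; the stated summary does not use them.

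The definitions raise a separate counting problem. If an episode fits neither class, it may be recorded inconsistently or not at all, whatever summary is used. The unclassified episodes lie between mild and severe, at the lower edge of an event that the safety objective names.

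**Working it through.** **Inputs from the article:** 12 weeks of treatment; 15 enrolled and 12 expected to complete per arm in the pilot; ages 8 to 17. The article states no hypoglycemia rate, proportion or power, so there is no figure of its own to reproduce. All rates below are assumptions, shown over a range.

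**Step 1. Proportion with at least one mild episode.** Take a weekly rate r, so the mean count over 12 weeks is m = 12r.

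- Poisson: P = 1 − exp(−m).
- Negative binomial, with variance m + k·m² to allow children to differ: P = 1 − (1 + k·m)^(−1/k).

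For r = 0.5, m = 6, and 12 if the rate doubles. Poisson gives 1 − exp(−6) = 99.8% and 1 − exp(−12) = 100.0%. With k = 1 the results are 1 − 1/7 = 85.7% and 1 − 1/13 = 92.3%.

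| Assumed control rate per week | Model | Control | Rate doubled | Shift (points) |
|---|---|---|---|---|
| 0.05 | Poisson | 45.1% | 69.9% | 24.8 |
| 0.05 | k = 1 | 37.5% | 54.5% | 17.0 |
| 0.1 | Poisson | 69.9% | 90.9% | 21.0 |
| 0.25 | Poisson | 95.0% | 99.8% | 4.7 |
| 0.25 | k = 1 | 75.0% | 85.7% | 10.7 |
| 0.5 | Poisson | 99.8% | 100.0% | 0.2 |
| 0.5 | k = 0.5 | 93.8% | 98.0% | 4.2 |
| 0.5 | k = 1 | 85.7% | 92.3% | 6.6 |

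The control proportion reaches 95% at about 0.25 per week under Poisson (12r = ln 20 ≈ 3.0), but only at about 1.6 per week with k = 1 (12r = 19).

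**Step 2. What is lost with 12 per arm.** The article names no test for adverse events, so this only compares the information in the two summaries. For a doubling from 0.5 per week, Fisher's exact test on the proportions has power 0.000 (Poisson), 0.000 (k = 0.5) and 0.008 (k = 1). A t test on square-root counts (20,000 simulations) has 0.997, 0.49 and 0.28. From 0.05 per week under Poisson, the figures are 0.14 and 0.31.

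**Step 3. Severe events.** At assumed rates of 0.05 to 0.2 per child-year, P = 1 − exp(−rate × 12/52) = 1.1% to 4.5% of controls. The chance of no event among 15 controls is 84% to 50%. These proportions are near zero, not near 100%.

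**Step 4. The definitions side by side.** Take a symptomatic episode with glucose below 4 mmol/L.

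- The child can self-treat: mild.
- The child needs help because of reduced consciousness, or has a seizure: severe.
- The child is conscious, has no seizure and cannot self-treat: neither.

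The third case is foreseeable with enrollment from age 8.

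**The case against.** - **The article is condensed, and an analysis plan may summarise the weekly frequencies.** That is possible, and the Analysis section does not exclude it. But the article is not silent on adverse events: it fixes a summary for all of them, and that summary does not match how mild hypoglycemia is collected.
- **A reader might infer that the main safety comparison saturates near 100% in both arms and cannot show a rise.** The documents do not support this. The safety objective names severe hypoglycemia and DKA. For severe hypoglycemia the limit is few events in 12 to 15 children per arm, as Step 3 shows, and a rise would still appear in a proportion.
- **Even for mild episodes, saturation is conditional.** It needs a rate that the article does not give, little variation between children, and a reading of the proportion as participants with at least one episode, which the sentence does not state. At low rates it fails. This objection stands, and it limits the point to what may be hidden if episodes are common.
- **A reader might infer that any conscious child helped by a parent goes uncounted.** The mild definition says "able to self-treat with oral rapid-acting carbohydrate", which describes ability. A capable child who is helped anyway is still mild; only a child unable to self-treat is left out. Requiring a glucose reading for a severe event is a choice of definition, not a contradiction.
- **A count analysis is weak at this size.** This is correct if children differ much: power for a doubling at 0.5 per week is then 28% to 49%. A rate with an interval is still more informative than the proportion, but it will be imprecise.

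**Conclusion.** The point holds in a limited form. The stated summary does not use the frequency data that the article sets out to collect on mild hypoglycemia. If the proportion counts participants with at least one episode and mild episodes are common, a doubling could go largely unseen: a shift of 0.2 to 6.6 percentage points at an assumed 0.5 per week, depending on how much children differ. If episodes are rare, the shift is about 17 to 25 points at 0.05 per week and the proportion does respond. Proportions, with event counts, are suitable for severe hypoglycemia and DKA. The gap in the definitions rests on no assumed rate: it follows from the wording, and is confined to conscious children without a seizure who cannot self-treat.

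**What to change.** 1. In the Analysis section, report mild hypoglycemia as episodes per participant-week by arm, with a rate ratio and 95% confidence interval from a simple count analysis robust to overdispersion. Add baseline frequency as a covariate if the sample allows.
2. State whether the denominator of each adverse-event proportion is participants or events. Keep proportions, with event counts, for severe hypoglycemia and DKA.
3. In the Intervention section, ask the investigators to reconcile the mild and severe definitions so that every recorded episode is counted exactly once. Where the clinical boundary lies is for them to decide.

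The cost is one more descriptive analysis, imprecise with 12 to 15 per arm, and a small change to the diary. The frequencies are already to be collected.
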